### Randomisation and blinding

Participants are randomised between duloxetine (n=54) and placebo (n=27). The allocation ratio is 2:1; given that around half of the population undergoing active treatment is expected to have satisfactory pain relief, this should result in approximately equal numbers between groups of placebo intakes, responders and non-responders. A block randomisation, with block sizes of 9 and 2, is utilised and was generated by the Clinical Trials Pharmacy (CTP) at Nottingham University Hospitals (NHS Trust) using a pseudo-random algorithm at http://www.randomization.com. The allocation list is kept by the CTP in a password-protected file. Investigators may identify the treatment for each participant via request to the CTP; however, during treatment, this breaking the code procedure may only be done in the event of a medical emergency when treatment is dependent on knowledge of the actual drug received. In case the treatment code for a participant is broken or other actions, such as recording date or reasons for breaking the blind, discontinuation of trial treatment must be reported to the sponsor (University of Nottingham).

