### Sample size estimation

The sample size calculation was performed according to the guidelines stated by Lenth and colleagues.^34^ Estimates of change in functional activation were deduced from a duloxetine intervention study (effect size was calculated based on p values provided for the ACC).^17^ Using the Java applets,^35^ it was estimated that a one-sample, one-tailed, t-test would have 80% power at alpha of <0.005 (to allow for 10 multiple independent tests) with approximately 19 participants per group: responders to duloxetine treatment, non-responders and placebo groups.

Based on previous experience of non-usable imaging data due to patient and/or technical factors in 10% of cases, a sample size of >22 participants per group was necessary. A further allowance for 20% dropout gives 27 participants in each group, resulting in a recruitment target of 81 participants. The study is not be powered to assess clinical efficacy.

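### The stated block sizes of 9 and 2 are not compatible with the stated 2:1 allocation (54:27), because a block of 2 cannot hold a 2:1 split

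*Protocol article*

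**What the plan says.** All the conflicting statements stand in one paragraph of the protocol article, Randomisation and blinding. On the split: "Participants are randomised between duloxetine (n=54) and placebo (n=27). The allocation ratio is 2:1". On the method: "A block randomisation, with block sizes of 9 and 2, is utilised". The Abstract repeats the 2:1 allocation.

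The same paragraph gives the reason for the ratio. About half of the treated participants are expected to respond, and "this should result in approximately equal numbers between groups of placebo intakes, responders and non-responders". Sample size estimation then sizes the trial on those three groups, "with approximately 19 participants per group: responders to duloxetine treatment, non-responders and placebo groups", and inflates this to 27 per group and 81 in total for unusable scans (10%) and dropout (20%).

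The article does not say how a block of 2 is divided between the arms, how many blocks of each size the list contains, or that some blocks follow a different ratio.

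**The concern.** In permuted-block randomisation the allocation ratio is built into each block, so the block size has to be a multiple of the sum of the ratio's terms. For 2:1 that sum is 3. Nine qualifies and two does not. As written, the rule cannot be followed and also be relied on to give the stated arm sizes.

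The ratio matters more here than in most two-arm trials. The treatment-mechanism primary outcomes are measured in duloxetine responders, and the response-prediction outcome compares responders with non-responders at baseline. All these participants come from the duloxetine arm. Each block of 2 split 1:1 pulls the list away from 2:1 at that arm's expense, and the planned numbers leave very little margin over the required group size.

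A secondary matter is predictability. In a 1:1 pair the second place is determined once the first is known.

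**Working it through.** **Inputs.** From Randomisation and blinding: arms of 54 and 27, ratio 2:1, block sizes 9 and 2, and about half of treated participants responding. From Sample size estimation: about 19 evaluable per group, 10% unusable imaging, 20% dropout, 27 per group, 81 in total.

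**1. The plan's own figures reproduce.** Retained fraction = 0.9 × 0.8 = 0.72, a loss of 28%. Then 19 / 0.72 = 26.4, rounded up to 27, and 3 × 27 = 81. At 2:1, 81 × 2/3 = 54 and 81 × 1/3 = 27. Nine blocks of 9 at 6:3 give 9 × 6 = 54 and 9 × 3 = 27. The total and the split are therefore sound, and the difficulty lies in the block-size statement.

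**2. Can each block size hold 2:1?** Block of 9: 9 × 2/3 = 6 and 9 × 1/3 = 3, whole numbers. Block of 2: 2 × 2/3 = 1.33 and 2 × 1/3 = 0.67, not possible. A block of 2 can be 1:1, or 2:0 or 0:2. The last two involve no randomisation within the block.

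**3. Effect on a list of 81 made of complete blocks.** Let *a* be the number of blocks of 9 (6:3) and *b* the number of blocks of 2 (1:1), with 9*a* + 2*b* = 81. Duloxetine D = 6*a* + *b* and placebo P = 3*a* + *b*, so D − 2P = −*b*. The 2:1 ratio holds only when *b* = 0. Expected usable responders = D × 0.72 × 0.5, taking 50% response and 28% loss.

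| Blocks of 9 | Blocks of 2 | D:P | Ratio | Expected usable responders |
|---|---|---|---|---|
| 9 | 0 | 54:27 | 2.00 | 19.4 |
| 7 | 9 | 51:30 | 1.70 | 18.4 |
| 5 | 18 | 48:33 | 1.45 | 17.3 |
| 3 | 27 | 45:36 | 1.25 | 16.2 |
| 1 | 36 | 42:39 | 1.08 | 15.1 |

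The case nearest to the plan is 51:30, a shift of three participants from duloxetine to placebo and a loss of 19.4 − 18.4, about one expected usable responder.

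**4. If both sizes are drawn with equal probability (an assumption).** An average pair of blocks contributes 6 + 1 = 7 duloxetine and 3 + 1 = 4 placebo, a long-run ratio of 7:4 = 1.75. Simulated lists stopped at 81 average about 51.5:29.5, which gives 51.5 × 0.72 × 0.5 = 18.5 expected usable responders.

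**5. Exceptions.** Outside complete blocks with 1:1 pairs, 54:27 can still arise. Eight blocks of 9, one block of 2 and the first seven places of a further block of 9 falling 5:2 give 48 + 1 + 5 = 54 and 24 + 1 + 2 = 27. In the simulation of step 4, exactly 54:27 came up in about 2.4% of the lists that used a block of 2. Deliberately unequal pairs could also reach it: with seven blocks of 9 and nine blocks of 2, 12 of the 18 places in the pairs would have to be duloxetine. The article describes neither arrangement.

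**The case against.** The strongest reply is that this is a wording problem with little consequence. Nine blocks of 9 reproduce 54:27 exactly, so the 2 may be a misprint or may have been meant as something other than a block length. The article does not say how many blocks of 2 were used, if any. That stands: the text shows a contradiction, not a misallocated trial. A reader might infer that 54:27 is impossible once any block of 2 is used, but step 5 shows that this is strict only for complete blocks with 1:1 pairs.

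The likely effect is also small. The nearest case costs about one expected usable responder. Chance alone moves that count more: with 54 participants and probability 0.72 × 0.5 = 0.36, the standard deviation is √(54 × 0.36 × 0.64) ≈ 3.5. The article promises only approximate equality of the groups, and a drift in the ratio does not in itself bias a within-responder change or a responder versus non-responder comparison. All of this stands, and it limits the severity. It does not remove the conflict, since nothing in the article reconciles a block of 2 with a 2:1 ratio.

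A reader might also infer that concealment is compromised, because participants learn their allocation at the end of follow-up and the article says "Investigators may identify the treatment for each participant via request to the CTP", limiting such requests to medical emergencies only during treatment. The documents do not support that. The text under Figure 1 keeps researchers blinded until acquisition has finished, and the end-of-study disclosure is made to the participant alone, by pharmacy staff with no part in the research procedures or analysis. The list is held in a password-protected pharmacy file. To use a pair, a recruiter would have to know where it falls in the list and learn its first allocation before the second person enters. No route to this is described.

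**Conclusion.** The concern holds as an internal contradiction: a 2:1 allocation of 54:27 is not compatible with block sizes of 9 and 2. Either the block sizes are misreported or the list does not follow the stated ratio, and the article alone cannot show which.

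If blocks of 2 were used, complete and split 1:1, the smallest departure is 51:30. Expected usable responders then fall from just above the required figure of about 19 to just below it, assuming 50% response and 28% loss. Larger departures such as 48:33 need many blocks of 2 (18 of them, against five blocks of 9), and nothing in the article points to that.

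Severity is moderate. A randomisation rule is wrong as written in a trial that is still running, but the plausible numerical effect is small and no allocation failure has been demonstrated. Predictability of the second place in a pair is a secondary concern, conditional on 1:1 pairs actually existing in the list.

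**What to change.** The Clinical Trials Pharmacy, which generated and holds the list, should check the block sizes actually used without unblinding the investigators. The next step depends on the result.

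- **No blocks of 2 in the list.** Correct the stated block sizes. The list, the ratio and the sample size stay as they are.
- **Blocks of 2 in the list.** Leave allocations already made unchanged. Generate the unused remainder with block sizes in multiples of 3 (for example 3, 6 and 9), each split exactly 2:1. Restate the allocation ratio and the expected placebo, responder and non-responder numbers actually delivered, so that they can be set against the requirement of about 19 per group.

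The cost in the first case is a short pharmacy check and a wording correction. The second adds a controlled regeneration of the unused part of a live list, documented by the pharmacy, and should be undertaken only if the check shows that it is needed.

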**Figure 1 F1:**
[figure not shown]
Participation timeline and general characteristics of each study visit. QST, quantitative sensory testing.

Participants are assigned, by the investigators, a unique identification number (sequentially numbered) and attend the university twice, for both a baseline and follow-up visits. Treatment consists of 6 weeks of taking either duloxetine capsules or placebo equivalent, followed by 2 weeks of dose reduction for those taking duloxetine to minimise drug withdrawal effects (figure 1). To minimise potential side effects, participants take one tablet (duloxetine 30 mg) daily during 2 weeks prior to switching to the target dose of 60 mg/day. Both researchers and participants are blinded to the treatment allocation until data acquisition is complete. At the end of the follow-up visit, individual allocation is disclosed to the participant only by one of the CTP staff members who are not involved in the any data analysis or research procedures. Data analysts will be blinded to treatment allocation.

Individual participation in the study is for around 8 weeks, starting with signing informed consent and ending with the conclusion of the drug reduction phase.

**Figure 2 F2:**
[figure not shown]
Details of experimental testing and randomisation of participants. Volume of interest for magnetic resonance spectroscopy is located in the midanterior cingulate cortex. ASL, arterial spin labelling; CPM, conditioned pain modulation; fMRI, functional MRI;  OA, osteoarthritis; PPT, pressure pain thresholds; QST, quantitative sensory testing; Question, questionnaires; rsfMRI, resting state fMRI; T1w, T1-weighted MRI; TS, temporal summation.

### Experimental testing

The experimental testing is primarily based on multimodal neuroimaging and QST, in conjunction with questionnaire assessment and genetics. This should provide a broad evaluation of the multifaceted nature of pain, assessing both central and peripheral mechanisms, as well as psychological and cognitive traits, among others, which should allow pinpointing precise phenotyping of patients into distinct groups. Time points and types of data being collected are summarised in figure 2 and details of questionnaires are given below.

Questionnaires:PainDetect (baseline)—a screening questionnaire to identify neuropathic components of pain.^19^
Pain Catastrophizing Scale (PCS) (baseline)—a 13-item scale to measure pain catastrophising, which can be split into three subscales named rumination, magnification and helplessness.^20^
State-Trait Anxiety Inventory (STAI) (baseline)—a psychological inventory assessing anxiety. It contains 40 items and can be split into two subscales being state anxiety and trait anxiety.^21^
Beck Depression Inventory II (BDI) (baseline)—a 21-item multiple-choice self-report scale for measuring the severity of depression.^22^
The intermittent and constant pain score (ICOAP) (baseline and follow-up)—an 11-question scale to characterise pain in individuals with osteoarthritis pain. It gives two subscales relating to intermittent and constant experience of pain.^23^
The Pain Sleep Questionnaire (baseline)—a five-item tool to assess the impact of pain on sleep.^24^
Brief Pain Inventory (BPI) (daily)—a nine-item questionnaire for measuring the severity of pain and the impact of this pain on daily functioning. The severity subscale is used to define the response definition (below).^25^
Mini-Cog (baseline)—contains a three-item recall test and a clock drawing test to screen cognitive impairment.^26^
Educational level (baseline).Questions on belief (baseline)—consist of four questions to assess an individual’s expectations on treatment and medical care.^27^

Participant general details:Age.Sex.Pain intensity (measured on a numeric rating scale ranging from 0 to 100, where 0 represents no pain at all and 100 stands for excruciating pain).Pain duration.Analgesia intake (last 24 hours).Caffeine intake (last 24 hours).Average daily caffeine intake.Average weekly alcohol intake.Medication.

Other:10 mL blood samples.Analgesia diary (daily).

### Response definition

Response to duloxetine is defined as a 50% reduction in the severity of ongoing pain from baseline to end of treatment, as measured by the BPI severity subscale. This threshold was chosen based on previous randomised controlled trials of duloxetine in osteoarthritis.

### Primary outcomes

#### Treatment mechanism

Change in the regional response of BOLD contrast to pinprick nociceptive stimulation after duloxetine treatment (MRI2) versus baseline (MRI1) in treatment responder group.Functional connectivity change from baseline (MRI1) to post duloxetine treatment (MRI2) using network metrics of BOLD fMRI under resting condition in treatment responder group.

#### Response prediction

Differences in nociceptive BOLD response and network function at baseline between responders and non-responders.

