**Methods and analysis:**

This is an ongoing single-centre randomised placebo-controlled mechanistic study (2:1 (placebo) allocation), using a multimodal neuroimaging approach, together with psychophysiological (quantitative sensory testing), genetics and questionnaire assessments. Eighty-one subjects with chronic knee OA pain are planned to power for between-group comparisons (placebo, duloxetine responder and duloxetine non-responder). Participants have a baseline assessment and, following 6 weeks of duloxetine (30 mg for 2 weeks, then 60 mg for 4 weeks), a follow-up evaluation. Brain imaging is performed at 3T with blood-oxygen-level dependent functional MRI at rest and during pin-prick nociceptive stimulation for main outcome assessment; arterial spin labelling and structural imaging (T1-weighted) for secondary outcome assessment. Questionnaires evaluate pain, negative affect, quality of sleep and cognition.

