## Primary objectives

The objective of this study is to identify a functional change in brain signature indexing the analgesic mechanism of duloxetine and to identify brain imaging and psychophysical markers that predict the response to duloxetine treatment.

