## Main hypotheses

Analgesic response to duloxetine treatment can be predicted using a range of baseline brain imaging markers and QST.Analgesic response to duloxetine is mediated by modulation of neural networks underpinning emotional control.Duloxetine-induced changes in brain activation differ between responders and non-responders.

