#### Secondary outcomes

Difference in the regional response of BOLD contrast to pinprick nociceptive stimulation after duloxetine treatment (MRI2) between responder and non-responder groups.Functional connectivity differences post duloxetine treatment (MRI2) using network metrics of BOLD fMRI under resting condition between treatment responder and non-responder groups.Correlation between baseline CPM and TS with brain activity and connectivity changes from baseline to post 6 weeks of duloxetine treatment (rsfMRI and pinprick fMRI).Group differences in brain activity (pinprick fMRI and rsfMRI) and structure (T1-weighted brain MRI) in pain processing, limbic and modulatory pathways changes from baseline to following 6 weeks of duloxetine treatment, in comparison to placebo.Identification of baseline QST (CPM, TS, PPT) and questionnaire parameters (BDI, STAI, PCS, ICOAP) that predict response to duloxetine.Multivariate treatment response prediction model.

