### Data analysis

Clinical, QST and psychometric data will be compared between groups and conditions using the latest versions of statistical and image analysis software including SPSS (version 21.0).

Brain imaging data will be analysed using the latest versions of several established toolboxes: FSL (FMRIB Software Library),^28^ PyMVPA (Multivariate Pattern Analysis),^29^ Statistical Parametric Mapping V.8 (London, UK), REST (Resting-State fMRI Data Analysis Toolkit), Brain Connectivity Toolbox and GRETNA (Graph Theoretical Network Analysis)^30–32^ and LCModel (Linear Combination Model) for MRS data.^33^ All data will undergo established quality control and standard recommended preprocessing. Preprocessing steps for functional data include motion correction, slice-timing correction using Fourier-space time-series phase-shifting, non-brain tissue removal, spatial coregistration to T1-weighted image and normalisation to the MNI anatomical standard space. Spatial smoothing will be carried out using an isotropic Gaussian kernel and a high-pass temporal filtering will be applied. Next, for task-related fMRI, statistical maps will be generated for contrasts of interest, such as to identify brain activity evoked by pinprick in each individual scan using first-level general linear model.

Z-scores will be extracted from regions of interest of pain processing nodes defined from meta-analysis,^7^ emotion regulatory, default mode and salience network including anterior cingulate cortex, anterior insula, amygdala, brain stem and thalamus for both task-related and resting functional maps. Individual functional connectivity maps will be also generated. These will be used on higher level analysis which will include, among others: (1) Paired t-test to evaluate treatment effects; (2) two-sample t-test to compare groups (responders and non-responders) at baseline; (3) correlation analysis to determine associations with psychometric and QST measurements.

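### The primary response-prediction contrast lies wholly within the duloxetine arm, so it can identify who improves on duloxetine but not who improves because of it

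*Protocol article*

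**What the plan says.** All references are to the protocol article.

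- **Aim.** Primary objectives includes the aim "to identify brain imaging and psychophysical markers that predict the response to duloxetine treatment". Main hypotheses states: "Analgesic response to duloxetine treatment can be predicted using a range of baseline brain imaging markers and QST".
- **Outcome.** Under Primary outcomes, Response prediction reads "Differences in nociceptive BOLD response and network function at baseline between responders and non-responders".
- **Who is a responder.** Response definition: "Response to duloxetine is defined as a 50% reduction in the severity of ongoing pain from baseline to end of treatment", measured on the BPI severity subscale. No responder status is defined for placebo participants.
- **Groups.** The abstract, Randomisation and blinding, and Sample size estimation all work with three groups: placebo undivided, and the duloxetine arm split into responders and non-responders. The 2:1 allocation (54 v 27) is chosen to make these three about equal.
- **Test.** Data analysis names a "two-sample t-test to compare groups (responders and non-responders) at baseline".
- **Placebo.** The only outcome that names placebo is a secondary one. It concerns change in brain activity and structure over six weeks, not prediction from baseline.
- **Other predictors.** Secondary outcomes also lists baseline QST and "questionnaire parameters (BDI, STAI, PCS, ICOAP) that predict response to duloxetine", and a multivariate prediction model. No analysis set is named for either.

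**The concern.** A 50% fall in pain while taking duloxetine is not the same as a 50% fall caused by duloxetine. The fall can also come from placebo response, natural fluctuation or regression to the mean, and Concomitant medication allows as-needed rescue analgesia as well. A baseline feature linked to any of these will differ between responders and non-responders even if it has nothing to do with the drug.

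Separating a marker of general improvement from a marker of drug benefit needs a comparison with people who did not receive the drug. The trial has such people, randomised and scanned at baseline, but no stated prediction analysis uses them. At stake is the conclusion on a primary outcome: a marker of non-specific improvement could be reported as a predictor of response to duloxetine.

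**Working it through.** **1. The plan's own figures.** Sample size estimation starts from 19 evaluable per group, 10% unusable imaging and 20% dropout: 19 / 0.9 / 0.8 = 26.4, rounded up to 27, and 3 × 27 = 81. The target reproduces. The point here concerns the meaning of the contrast, not this number.

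**2. Is the contrast really within one arm?** The Response prediction outcome does not say so itself. But response is defined as response to duloxetine, the three groups leave placebo undivided, and the allocation ratio is built on splitting the duloxetine arm. Together these leave no other natural reading.

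**3. How much non-drug response could the responder group contain?** Let p1 be the response probability on duloxetine and p0 that on placebo, by the same definition. The share of duloxetine responders who would also respond on placebo lies between max(0, p0 + p1 − 1) / p1 and min(p0, p1) / p1. The inputs are p1 = 0.50 (the article's expectation, which it states for satisfactory relief and does not tie to the BPI threshold) and p0 = 0.20 to 0.35 (an assumption).

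| p0 | lower bound | upper bound | upper bound × 27 responders |
|---|---|---|---|
| 0.20 | 0 (0.70 − 1 < 0) | 0.20/0.50 = 40% | 10.8 |
| 0.35 | 0 (0.85 − 1 < 0) | 0.35/0.50 = 70% | 18.9 |

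The upper bound is reached only if everyone who would respond on placebo would also respond on duloxetine.

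**4. What the planned test does with a non-specific marker.** This is a simulation on assumed inputs (6,000 trials per setting): 38 evaluable on duloxetine and 19 on placebo, response 50% and 30%, two-sided alpha 0.005. Improvement = arm mean + r × marker + √(1 − r²) × noise, with the same r in both arms, so the marker has no drug-specific role. The planned test compares the marker between duloxetine responders and non-responders. The interaction test regresses continuous improvement on arm, marker and marker × arm.

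| r | planned t-test significant | interaction significant |
|---|---|---|
| 0 | 0.7% | 0.3% |
| 0.3 | 8.7% | 0.6% |
| 0.5 | 38% | 0.6% |
| 0.6 | 62% | 0.5% |

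**5. The same tests when the marker acts only under duloxetine** (r = 0 on placebo).

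| r on duloxetine | planned t-test significant | interaction significant |
|---|---|---|
| 0.5 | 38% | 17% |
| 0.6 | 64% | 32% |
| 0.7 | 86% | 50% |

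At r = 0.5 the planned test is significant in 38% of trials in both situations. It must behave alike in both, because the duloxetine data are generated identically; only the placebo arm differs. The interaction tells the two apart, but with low power.

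**6. Precision cost.** With equal marker variance in the arms, the ratio of the interaction's standard error to that of the duloxetine-only slope is √(1 + n_dulox / n_placebo).

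- After both losses: 54 × 0.9 × 0.8 = 38.9, about 39, and 27 × 0.9 × 0.8 = 19.4, about 19. Ratio √(1 + 39/19) = 1.75.
- With all usable baseline scans: 54 × 0.9 = 48.6 and 27 × 0.9 = 24.3. Ratio √(1 + 48.6/24.3) = 1.73.

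The second line is a best case, since it needs an end-of-treatment BPI from everyone with a usable baseline scan.

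**The case against.** **The article is condensed and its list of analyses is open-ended.** A placebo-arm or interaction analysis may sit in the full protocol or an analysis plan. This stands as a limit on scope. A reader might infer that placebo participants are excluded from the QST, questionnaire and multivariate predictors as well; the article does not say so, because it names no analysis set for them. It does not rescue the primary outcome, whose groups and test are both stated.

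**The size is uncertain.** A reader might infer that 40% to 70% of responders would have improved anyway. The documents do not support that. The placebo rate is assumed, the 50% is not tied to the BPI threshold, and without the assumption that placebo responders also respond on duloxetine the share could be as low as zero. This stands; the figures are ceilings under stated assumptions.

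**The study is mechanistic and was not sized for an interaction.** A reader might infer that the interaction should replace the primary test. At 17% to 50% power on the assumptions above, it would often miss a true drug-specific predictor, and a primary outcome of an ongoing registered trial would have been changed to obtain it. This also stands, and is why the interaction is proposed as a supporting analysis. Low power for the drug-specific question does not, however, turn the within-arm contrast into an answer to it.

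**The contrast is valid for what it measures.** Agreed: it identifies baseline features associated with improvement on duloxetine. The fault lies in the conclusion attached to it.

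**Conclusion.** The concern holds for the primary response-prediction outcome. As fixed in the article, the analysis is prognostic within one arm, while the objective and hypothesis call for prediction of response to duloxetine. The conclusion does not follow from the test, and this rests on the stated groups and test, not on missing detail.

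The size cannot be fixed from the documents. With 50% response on duloxetine and an assumed 20% to 35% on placebo, up to 40% to 70% of duloxetine responders could have responded on placebo, the maximum requiring that all placebo responders would also respond on duloxetine. In the simulation, a marker with no drug-specific role but a correlation of 0.3 to 0.6 with improvement passes the planned test in about 9% to 62% of trials. Both the correlations and the 30% placebo response used there are assumptions.

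For the QST, questionnaire and multivariate predictors the finding is narrower: the article claims prediction of response without stating how, or whether, placebo enters.

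**What to change.** 1. Keep the planned responder v non-responder contrast, but word its conclusion as prognostic: baseline features associated with improvement while taking duloxetine.
2. Apply the same BPI severity measure to the placebo arm.
3. Prespecify, before allocation is released to the analysts, a supporting model: end-of-treatment BPI severity on baseline BPI severity, arm, marker and marker × arm. Include all randomised participants with a usable baseline scan (MRI1) and an end-of-treatment BPI. Report the interaction with its confidence interval.
4. Claim a duloxetine-specific predictor only if that interaction supports it.
5. State the analysis set and the same rule for the QST, questionnaire and multivariate predictors.

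No new data are needed: BPI is recorded daily, both arms have the baseline scan, and Compliance provides for postal follow-up questionnaires when a participant cannot return. Those who are withdrawn may still lack an end-of-treatment BPI. The primary outcome and sample size stay as they are.

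The price is precision. The interaction's standard error is about 1.75 times that of the duloxetine-only slope (1.73 on the MRI1 set), so an inconclusive interaction is likely even for a real drug-specific marker, and claims about drug-specific prediction will be more cautious.
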